# A novel way to understand and communicate the burden of AntiPsycHotic prescribing for adults across specialist Intellectual Disability services in England and Wales: the APHID feasibility study protocol

**DOI:** 10.3389/frhs.2025.1393805

**Published:** 2025-05-09

**Keywords:** intellectual disability, learning disability, antipsychotic, psychotropic, overprescribing

## Abstract

**Background:**

The stopping overmedication of people with a learning disability, autism, or both (STOMP) programme was launched in 2016 in response to concerns about the over-prescribing of medication in people with intellectual disability. The programmes focus has been on the withdrawal of antipsychotic treatment for the individual person than the service or dosage optimisation. It could be that cumulative service level antipsychotic treatment converted and presented as chlorpromazine units could allow for comparison of services on how antipsychotic treatment is being utilised and allow for comparing of practices between services in different regions. The aim of this feasibility study is to explore if cumulative service scores of antipsychotic treatment burden could define prescribing patterns across different specialist intellectual disability services in England and Wales, focused on those on ≥2 antipsychotic treatments. There is no evidence to use ≥2 antipsychotic treatments for any individual.

**Methods:**

The study is a feasibility cross-sectional study investigating service antipsychotic treatment cumulative burden at seven annual time points, 2017–2023. De-identified data for adult patients with intellectual disability under the care of specialist intellectual disability services in receipt of ≥2 oral and/or long-acting IM (intramuscular) injectable (depot) antipsychotic treatments are included. Demographic and clinical data will be collated, in addition to information on the prescribed antipsychotic treatments. The data will be evaluated for data completeness and will be inputted into the Statistical Process Control tool. Outcomes will be measured using a combination of methods including descriptive analysis (including mean, standard deviation and percentage values), and a mixed effects regression model, to determine changes in chlorpromazine equivalent dose values over time.

**Results:**

Seven England and Wales National Health Service intellectual disability services are recruiting up to 490 people. There were recognised challenges in identifying the relevant eligible cohort across services and administering a common set of outcome measures.

**Discussion:**

This study is intended to inform decisions to design a wider registry that would involve antipsychotic treatment prescribing data for patients across multiple sites nationwide. Developing a de-identified database using routinely collected data, without the requirement for informed consent, comes with unique benefits and challenges.

**Registry reference:**

NCT06238089 (www.clinicaltrials.gov).

## Introduction

Intellectual Disability (ID) is defined by significant limitations in both intellectual functioning and adaptive behaviour originating prior to adulthood (1). The global prevalence of ID is approximately 1% (2). In the United Kingdom (UK) approximately 17.5% of PwID are prescribed APTs (3). APTs are mainly used to treat mental health conditions such as schizophrenia and other psychoses, agitation, severe anxiety, mania and violent or dangerously impulsive behaviour. The prevalence of psychiatric disorders in those with severe ID is higher than in those with mild or no ID (4) and therefore the use of APTs in some cases is justified. Data from the records of 571 general practices in the UK showed that 71% of PwID treated with APTs did not have a record of severe mental illness (5). APTs can have adverse consequences, both in the short-term (e.g., sedation) and longer-term (e.g., diabetes, obesity). Thus, judicious prescribing is of paramount importance.

In 2016, National Health Service (NHS) England launched the stopping overmedication of people with a learning disability, autism, or both (STOMP) initiative, in response to concerns about overprescribing of psychotropic medications for PwID, particularly, APT, and especially outside the licensed indication for these medications (6).

Prior to the COVID-19 pandemic, national NHS digital data demonstrated a small reduction in APTs prescribed for PwID since the launch of the STOMP initiative (7). However, the COVID-19 pandemic had a profound impact on health outcomes across the world, with PwID experiencing a disproportionate impact (8). PwID often received reduced support relative to pre-pandemic times, with widespread difficulties in accessing medical, mental health, and social support services (9). Preliminary data taken from a limited sample of adults accessing specialist adult ID services across two England-based healthcare trusts suggested that the pandemic led to increased APT prescribing, particularly in areas more significantly impacted by the pandemic (i.e., those associated with a greater level of lockdown restrictions, as well as greater urbanisation) (10). In less specialised settings, a decrease in the prescribing of antipsychotics in PwID was observed (11). However, this did not account for antipsychotics that had been restarted, or doses that had been increased in the time period, or antipsychotics that may have been prescribed by secondary care services (11).

Previous NHS big data analyses of this issue highlight significant concerns but fail to provide a picture of what successful prescribing practices look like, as they tend to be principally focussed on prescribing prevalence rather than dose. APT burdens need to be measured according to medication doses to identify how and what is being prescribed and therefore identify the problems associated. First and second-generation APTs will be evaluated as they cause different side effects. First generation APTs cause significantly more extrapyramidal effects while second generation APTs are considered to have a greater risk of metabolic side effects (12). By recording the specific APTs that have been prescribed, the different prescriber preferences across the country can be examined and understood.

Previous research has tended to report on entire clinical populations of PwID, rather than a specific focus on those in receipt of ≥2 different forms of APTs, who are at greater risk (13). To date there is no clinical rationale or evidence to support two different APTs being prescribed (13). The study aims to determine if it is feasible to quantify multiple (≥2) APT prescribing in PwID as Chlorpromazine equivalent dose values (14), in specialist adult ID services across England and Wales between 2017 and 2023. Such potential data allows the comparison of prescribing patterns (including dosage levels) across specialist adult ID services in the UK over time. The 7-year period of data collection will allow the study of the data prior to the COVID-19 pandemic, during and for a short time after to observe the effects of this on prescribing by clinicians in these services.

Once the prescribing patterns of those receiving ≥2 APTs are further understood, it may allow for the opportunity to progress to obtain further understanding of the patterns across the country for those in receipt of one APT. It may also allow researchers to identify trends and patterns of variation, including measuring the impact of initiatives intended to improve patient care, such as STOMP.

The NHS England Statistical Process Control (SPC) tool (15) is an analytical technique that provides a validated means of plotting data over time. The SPC tool plots variation in data over time in a graphical format, helping better understand the impact of interventions and the most appropriate subsequent actions to take. The SPC tool operates in Microsoft Excel and requires extracted quantitative data to be manually entered, and also enables the user to enter upper and lower limits for expected data variation. This supports easier identification of any outlying data, with the tool also permitting annotation of any significant datapoints in the graphical output. In this study, it will be used to see if it enables researchers to track yearly APT prescribing among PwID receiving multiple forms of APT and monitor variation between services and patient groups. If this proves successful, then the SPC tool could be used to evaluate and measure ID specialist service use of APTs in PwID nationwide.

The study will help determine if mathematic dose conversion of APT and the use of the SPC can provide a readily understandable means to measure APT use across healthcare trusts, as well as within trusts over time. If this method is found to be successful for APT, similar methodology could be used to measure the burden of use of other families of psychotropic medications, such as antidepressants and benzodiazepines. As a result, this could provide a more comprehensive overview of psychotropic medication use among adults under the care of specialist adult ID services.

The study aims to help develop a novel, understandable approach to measuring APT burden on a local, national, and international level. This will help healthcare professionals, researchers, and policy developers understand the factors that contribute to overprescribing of APT medication (such as gender, ethnicity, nature of residence, level of ID and presence of co-occurring mental illness and/or other neurodevelopmental conditions), and develop targeted measures designed to mitigate such overprescribing. This study's findings will also provide a better understanding of the impact of the COVID-19 pandemic, and whether it did lead to a change in APT patterns. Where increased APT prescribing during the pandemic is observed in some healthcare trusts relative to others, factors contributing to such inter-trust differences can be explored.

Before similar methodology can be used to inform future studies, it is necessary to conduct this feasibility study to ensure that the study procedures allow the objectives to be met.

The feasibility objectives of the study are to evaluate whether it is:
(1)Feasible to identify PwID who have been prescribed ≥2 APTs over 7 years retrospectively.(2)Possible to obtain a complete data set for each patient identified and therefore be able to explore the prescribing patterns across the eight sites.(3)Feasible to quantify APT prescribing in PwID as Chlorpromazine equivalent dose values across different Healthcare Trusts in England and Wales.The main objectives of the study are to investigate:
(4)Yearly and overall prescribing patterns among PwID [with or without mental health reasons (co-occurring mental health conditions)] in receipt of ≥2 forms of APT over time.(5)How multiple APT prescribing has changed between 2017 and 2023 using chlorpromazine equivalent dose values, in PwID with mental health and no mental health indications.(6)The impact of the COVID-19 pandemic (and corresponding lockdown restrictions in England and Wales) on multiple APT prescribing among PwID.(7)Whether the SPC tool be utilised to track yearly APT prescribing among PwID receiving multiple forms of APT, and monitor variation between services (sites) and patient groups (e.g., psychiatric co-morbidities; challenging behaviour).

## Methods and analysis

### Study design

This is a multi-site cross-sectional study, involving data collection from specialist adult ID services based within eight NHS healthcare trusts across England and Wales over a seven-year time span (2017–2023). The eight trusts serve areas comprising of differing levels of urbanisation and pandemic-related lockdown restrictions to allow for the comparison of the impact of the COVID-19 pandemic on multiple APT prescribing among PwID.

The participating trusts are listed below, alongside their overall estimated catchment area:
•North East London NHS Foundation Trust (4.3 million) (16).•Cheshire and Wirral Partnership NHS Foundation Trust (1 million) (17).•Central and North West London NHS Foundation Trust (3 million) (18).•Cornwall Partnership NHS Foundation Trust (450,000) (19).•Coventry and Warwickshire Partnership NHS Trust (1 million) (20).•Hertfordshire Partnership University NHS Foundation Trust (400,000) (21).•Leicestershire Partnership NHS Trust (1.1 million) (22).•Swansea Bay University Health Board (390,000) (23).

### Patient eligibility criteria and identification

#### Inclusion criteria

Patients must satisfy all the following criteria to be enrolled in the study:
(1)Having received a psychiatric review by specialist adult ID services within the last year^1^(2)A diagnosis of ID(3)Being under the care of specialist adult ID services within the last year of the date of interest(4)In receipt of ≥2 APTs [oral and/or IM injectable (depots)]^1^For a patient to be included on 1st June 2017, data is to be extracted from the most recent psychiatric review within the period between 1st January 2017–31st December 2017.

#### Exclusion criteria

Patients who meet any of the following criteria will be excluded from study participation:
(1)Under the age of 18 years(2)Patients treated with ClozapinePatients treated with Clozapine are excluded from the study as the drug is primarily used to treat specifically treatment-resistant Schizophrenia, whereby patients have been insufficiently responsive and/or intolerant of other APTs (24). Therefore, there would be a high likelihood that a patient treated with Clozapine has an appropriate diagnosis. Furthermore, those prescribed Clozapine are more likely to receive a more enhanced service due to the drug's side effect profile and the requirement for frequent blood monitoring (24), which is likely to differ from most PwID who are prescribed other antipsychotics, who encountered a lack of physical health reviews during the COVID-19 pandemic (9).

This is a retrospective multi-centre cohort study whereby patients are de-identified at site and thus patient consent is not required. At each site, the direct clinical care team (consultant, trainee doctor or specialist nurse) or a research nurse will identify 7–10 adult ID patients on their caseloads for each of the census dates. The patients who were prescribed ≥2 APTs will be identified from the paper-based clinic letters, inhouse databases (e.g., clinical portal bespoke)/electronic systems (e.g., SystmOne, Rio, Care Notes). Data will be extracted from the patient's most recent clinic letter to the census date (1st July of specified year), either up to 6 months before or 6 months, i.e., for July 2017, between 1st January 2017 and 31st December 2017. See Figure 1 for the study flow chart.

**Figure 1 F1:**
[figure not shown]
Study flow chart.

A study ID will be generated from REDCap, and only the routine care team (or research nurse) will have access to the code and patient identifier, to perform repeat entry for the same record, if required. As the data will be anonymised (de-identified) at site by the clinical team, patient consent is not required. If a patient is identified in consecutive years as meeting the inclusion criteria, they will be recorded as a separate record, with a unique ID, as this is not a longitudinal study so patients will not be tracked over time.

### Outcome measures

Data for patients will be collected using standardised data entry forms, for each of seven consecutive years (2017–2023). Data collected (Table 1) will include basic demographic details (age, gender, ethnicity, residential circumstances), clinical data (ID classification, genetic variants, medical co-morbidities, epilepsy, neurodevelopmental conditions, neurodegenerative conditions, psychiatric co-morbidities, challenging behaviour), and data on the APT (first/second generation, dose, units, frequency, route of administration, reason for prescribing).

**Table 1 T1:** Data collection at each yearly time point (1st July 2017–2023).

			Timepoints yearly 01/07/2017–01/07/2023^a^
Caseload number on 2 or more antipsychotic treatments identified			
Date of nearest clinic letter			x
Demographics			
Age	Date of birth (month/year)		x
Gender	Male		x
	Female		x
	Gender non-conforming		
Ethnicity	Asian, Asian British, Asian Welsh		x
	Black, Black British, Black Welsh, Caribbean or African		x
	Mixed or multiple ethnic groups		x
	White		x
	Other ethnic group		x
Place of residence	Family home		x
	Residential home		x
	Supported living		x
	Living independently		x
	Other (describe)		x
ID classification			
ID classification	Mild		x
	Moderate/Severe/Profound		x
Genetic variants	Fragile X syndrome		x
	Down syndrome		x
	Tuberous sclerosis complex		x
	Developmental and/or epileptic encephalopathy		x
	Other		x
Clinical characteristics			
Co-occurring medical conditions^b^	Obesity		x
	Constipation (regular laxatives)		x
	Cerebral palsy and other paralytic syndromes		x
	Osteoporosis		x
	Epilepsy		x
	Metabolic syndromes	Diabetes	x
		Hypertension	x
		Dyslipidaemia	x
		Cardiovascular disease	x
	Other		x
Neurodevelopmental conditions	Autism spectrum disorder (ASD)		x
	Attention deficit hyperactivity disorder (ADHD)		x
Neurodegenerative conditions	Dementia		x
Co-occurring psychiatric conditions	Psychosis (Schizophrenia/schizoaffective disorder, bipolar affective disorder, severe depression with psychotic conditions or other		x
	Depressive disorders		x
	Anxiety disorders (obsessive compulsive disorder (OCD), Post-traumatic stress disorder (PTSD) or other		x
Challenging behaviour	Yes/no/not recorded		x
Antipsychotic drugs			
First generation APTs (most common brand name)^c^	Chlorpromazine (Largactil)—Levomepromazine (Nozinan)—Pericyazine (Neulactil)—Prochlorperazine (Stemetil)—Promazine—Trifluoperazine (Stelazine)—Benperidol (Frenactyl)—Haloperidol (Haldol)—Flupenthixol (Depixol; Fluanxol)—Zuclopenthixol (Clopixol)—Pimozide (ORAP)—Sulpiride		x
Second generation APTs (most common brand name)^c^	Amisulpride (Solian—oral route)—Aripiprazole (Abilify)—Asenapine—Cariprazine—Lurasidone—Olanzapine—Paliperidone—Quetiapine—Risperidone		x
Other^c^	Pipothiazine—Penfluoridol—Fluphenazine—Thioridazine—Other (free text)		x
Reason for each APT prescribed	Psychotic disorder		x
	To manage specific behavioural challenges/agitation		x
	To augment other psychotropic medication		x
	Anxiety disorder		x
	Other		x
	Not clearly indicated		x

^a^
Time-point: Most recent clinic letter to the 1st of July of the year under study; 6 months either side (e.g., 01/06/2017: between 1st January 2017 and 31st December 2017).

^b^
Co-occurring medical conditions, based on those most commonly reported in patients with ID.

^c^
Dose, units, frequency, and route of administration are recorded for each APT prescribed.

Data will be extracted from multiple sources for each patient by the clinical team. Source data will come from paper-based clinic letters, inhouse databases (e.g., clinical portal bespoke)/electronic systems (e.g., SystmOne, Rio, Care Notes). The yearly census date is the 1st of July and the patient's most recent information, and clinic letter will be identified (up to 6 months before or 6 months after the census date). Collected data will be anonymised at site by the clinical team and/or research nurses.

Data will be entered directly onto a study specific instance of REDCap (Research Electronic Data Capture), a secure web-based database. De-identified data will also be transferred on the SPC tool to evaluate and track the prescription changes over time. Only anonymised (de-identified) data will be available to the University of Plymouth research team/data processors for analysis. As the data is de-identified at site before being entered into the database, each year will be treated as independent even if patients are eligible year on year. There will be no patient linkage across time.

### Dose equivalent methods

To account for the different treatment doses of APT, data will be aggregated into a standardized form. Each patient's oral and long-acting IM injectable APT regime will be represented by their chlorpromazine equivalent dose values (14, 25), which offers a means of standardization for APT (14).

Chlorpromazine is a commonly used APT and a CPZ-equivalent dose is defined as a dose of antipsychotic that is comparable to 100 mg of CPZ. This is commonly used in clinical and research settings. It provides a universal language of APT burden that is readily understandable for healthcare professionals, researchers, policy makers, and the lay public alike.

There is no accepted standard for equivalence calculation and many methods have been documented with associated strengths and limitations. The study will utilise the Defined Daily Dose (DDD) equivalence method, highlighted in Leucht's 2016 paper, ‘Dose equivalents for antipsychotic drugs: The DDD method’ (25). This study acknowledges the limitations of all dose equivalence methods as highlighted by Patel et al. (26) including minimum effective dose, dose response curve, DDD and various consensus methods. The Leucht's DDD method, including equivalence tables, has been selected as a consistent approach to calculating equivalence. It always provides a method for comparing antipsychotic equivalence between first- and second-generation APTs. The authors highlight that this study is not intended to test equivalence methods, only to apply a consistent approach to calculation.

To facilitate conversion of APT to chlorpromazine equivalent dose values, a pre-programmed script in R/Stata will be utilised, following relevant conversion formulas [as per that included in the supplementary table that accompanies the Leucht et al. (25) article].

### Target sample size and justification

As this is a feasibility study no formal power calculation has been performed. The aim is for each site to collect between 7 and 10 patient's data per annum. Hence, the estimated study size will be approximately 392–600 patients for the seven-year period. It is estimated that there will be a high number of PwID receiving multiple oral and depot APTs each year which was estimated after discussion with the eight sites of their caseloads and the numbers expected on at least two oral and depots APTs and the duration they have been on review lists.

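### The upper end of the stated study size should be 560, not 600; the abstract gives a different site count and total without explanation; and both totals count yearly records, not people

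*Protocol article*

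**What the plan says.** The section Target sample size and justification states that "As this is a feasibility study no formal power calculation has been performed". It sets the collection rate: "The aim is for each site to collect between 7 and 10 patient's data per annum". From that rate it concludes that "the estimated study size will be approximately 392–600 patients for the seven-year period", and it describes the expected numbers as "estimated after discussion with the eight sites of their caseloads".

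The text under Exclusion criteria gives the same rate as an instruction to sites, which "will identify 7–10 adult ID patients on their caseloads for each of the census dates". Study design describes "data collection from specialist adult ID services based within eight NHS healthcare trusts across England and Wales over a seven-year time span (2017–2023") and lists eight trusts by name. The second feasibility objective in the Introduction also refers to eight sites.

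The Results paragraph of the abstract differs: "Seven England and Wales National Health Service intellectual disability services are recruiting up to 490 people".

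On the unit of count, the section on patient eligibility and identification says that a patient who qualifies in consecutive years is entered as a separate record with a new ID. Outcome measures adds that years are treated as independent and that patients are not linked over time. The Identification subsection of the Results acknowledges that one patient can count towards a site's target in several years.

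**The concern.** The study size is a simple product of three stated inputs, and one end of the range does not equal that product. The abstract then gives another total and another number of sites. A reader cannot tell whether the planned maximum is 490, 560 or 600, or whether the planned minimum is 343 or 392.

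The labels add to the difficulty. The sample size section counts patients and the abstract counts people, but the product counts site-by-year entries in which the same person may appear up to seven times. Someone who reads only the abstract would take 490 as a number of distinct individuals. What is at stake is an accurate description of the study's size, in value and in unit, in a feasibility study that is meant to inform a wider registry.

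**Working it through.** **Inputs**
- Records per site per year: 7 to 10 (Target sample size and justification; repeated under Exclusion criteria).
- Sites: 8 (Introduction objectives, Study design, Target sample size and justification), or 7 (abstract, Results).
- Annual time points: 7 (abstract, Methods; Study design).

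**Formula:** total = records per site per year × sites × years.

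| Sites | Lower end | Upper end | Stated in the article |
|---|---|---|---|
| 8 | 7 × 8 × 7 = 392 | 10 × 8 × 7 = 560 | 392–600 (sample size section) |
| 7 | 7 × 7 × 7 = 343 | 10 × 7 × 7 = 490 | up to 490 (abstract) |

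**Lower end, eight sites.** 392 reproduces exactly.

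**Upper end, eight sites.** The product is 560 against a stated 600. The gap is 600 − 560 = 40 records, and 40/600 = 6.7%. Changing one input at a time to reach 600 would need:
- 600/(8 × 7) = 10.7 records per site-year, above the stated maximum of 10; or
- 600/(10 × 7) = 8.6 sites; or
- 600/(10 × 8) = 7.5 years.

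None of these matches a stated input.

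**Abstract.** 490 reproduces exactly with seven sites. With eight, the same maximum rate gives 560, so the two totals differ by one site at the maximum (10 × 7 = 70 records).

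**Unit.** Each product counts entries per site per year. Since a patient eligible in several years is entered each time under a new ID without linkage, the number of distinct people is at most the number of records. The data as collected cannot show how far below that it lies.

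**The case against.** Four arguments on the other side deserve weight.

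1. *The range is described as approximate.* This softens the error but does not remove it. The lower end is exact to the unit, and the upper end exceeds what the stated maximum rate can produce.

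2. *The abstract's 490 is not an arithmetic error.* That is right. It stands in a Results paragraph in the present tense and may describe the services that were recruiting at submission. The article does not say so, however. Neither the Trial status section nor the account of set-up challenges mentions a withdrawn or unopened site. What stands is an unexplained inconsistency.

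3. *Recurrence of patients is disclosed.* It is, in three places in the body. The labels remain wrong, and the abstract read alone carries no such warning.

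4. *Nothing depends on the total.* This stands and limits the point. A reader might infer that these totals are denominators for the feasibility outcomes. The data analysis section does not support that: Objective 1 is a reported number, Objective 2 is a number and proportion with complete data among the patients concerned, and Objective 3 is a proportion of those identified at each site. A reader might also infer that a study in which every site met its maximum would be reported as falling short. It would not, because 560 lies inside the stated range and the article sets no threshold at 600. The instruction to sites, 7 to 10 per census date, is consistent and unaffected.

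A further tempting reading is that the study contains only a seventh as many people as it claims, for example 8 × 7 = 56 to 8 × 10 = 80 from eight sites. That would require every site to enter the same patients in all seven years. It is a theoretical floor that nothing in the article presents as expected, and the Identification subsection notes that discharge practice differs between services.

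**Conclusion.** The point holds as a minor correction to the stated sample size, with three parts:

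- The upper end of the range is wrong by 40 records (6.7% of 600). On the article's own inputs it is 560; the lower end of 392 is correct.
- The abstract's seven services and 490 conflict with the eight sites given in the Introduction, Study design and sample size section, and no explanation is offered.
- Both totals are yearly records labelled as patients or people.

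This assumes that the range was meant as the product of rate, sites and years. The wording of the sample size section implies this, and the exact match at 392 supports it. The documents do not show which site count is current. They also give no basis for an expected number of unique people. Whether treating the years as independent is a sound basis for the regression is a separate analysis question and forms no part of this conclusion.

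**What to change.** - In Target sample size and justification, state 392–560 patient-year records from eight sites. If only seven take part, state 343–490 from seven and say when and why the number changed.
- Use one site count in the abstract, objectives, Study design and sample size section. If the abstract is meant to report the sites recruiting at submission, say so and give the planned number beside it.
- Replace patients and people with records wherever these totals appear. Add one sentence saying that a person may contribute a record in more than one year and that, without linkage, the number of unique people cannot be determined.

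The cost is a text correction only. Site instructions, data collection and the planned analyses do not change.
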